#### Rejection criteria

Those found in the middle of the trial who failed to meet the case selection criteria; failure to complete the diet exercise in accordance with the regulations; failure to use drugs as prescribed, unable to judge efficacy or providing incomplete information; taking drugs that were prohibited and may affect the judgement of the effect.

#### Drop out criteria

Patients who must stop medication because of serious adverse drug reactions; patients who quit the trial due to ineffective treatment; patients who are unwilling to accept treatment or unable to complete follow-up due to poor compliance; patients who have no adverse reactions during treatment, but the treatment is interrupted due to other reasons, such as emigration and missing visits.

#### Termination criteria

Subjects who withdraw informed consent and request withdrawal from the study; pregnancy events occur during the study; side effects of drug or treatment operations are still intolerable; a situation in which the researcher deems it necessary for study withdraw.

If the participant meets the rejection criteria, they are removed, and the data will not be included in the final statistical analysis. However, the termination criteria are related to patients who may terminate during treatment, so the data from these patients will be included in the final statistical analysis.

### Informed consent

When selecting qualified participants, the researcher must describe the details of the clinical trial, including the purpose of the trial, the trial procedure, possible benefits and risks, and the rights and obligations of the subjects, so that the participants can completely understand and have sufficient time to consider. After their questions are answered satisfactorily, participants will sign the informed consent. When each participant signs an informed consent form, the doctor leaves his or her contact number with the participant, so he or she can contact the doctor at any time if conditions change.

### Randomization

After informed consent is obtained, participants will be randomly assigned in a 1:1 ratio to either an intervention (DDG combined with metformin) or a control group (placebo combined with metformin). Randomization will be performed by the Clinical Research Center of Longhua Hospital Affiliated to Shanghai University of Traditional Chinese Medicine.

#### Sequence generation

The method of central stratification and block randomization will be adopted. SAS software will be used to make a random sequence table to generate random numbers as drug numbers.

#### Allocation concealment mechanism

A specific statistical researcher who does not participate in the clinical trial will be responsible for generating the randomization sequence and distribute the number to the experimental products. The observer will remove the envelopes with corresponding serial numbers according to the order of each subject’s visit and distribute the drug according to the drug number, which will remain unchanged throughout the study.

### Blinding

The random distribution system will be implemented and managed by the Clinical Research Center of Longhua Hospital affiliated with Shanghai University of Traditional Chinese Medicine. The randomization code will be maintained by a specially appointed independent custodian. Researchers, participants, inspectors and data inputters will all be blind. The drug will be randomly coded according to the random scheme, and the coding number will become the unique identification code of the participants. According to the order of visits, subjects will be randomly divided into different groups. The dosage form and dose of the tested drug and the placebo are the same, and the drug will be uniformly packaged in the same drug label and distributed by the centre. The DDG placebo is prepared by the same manufacturer to ensure that the researchers and the patients do not have direct contact with the drug preparation and delivery process, so the double-blind method can be guaranteed. All participants and researchers in the trial will be asked to complete a questionnaire to evaluate the treatment at the last visit to assess the success rate of blinding [17].

### Sample size calculation

Our aim is to select an estimation method for sample size when comparing two sample means. When the number of samples is expected to be equal between the test group and the control group, the following formula can be used [18]:

$$n_C=\frac{\left(Z_{1-\alpha}+Z_{1-\beta}\right)^2\sigma^2\left(1+{\displaystyle\frac1K}\right)}{\left(\mu_T-\mu_C-\triangle\right)^2}$$

Here, *n*_*c*_ represents the estimated sample size of each test group, where *μ*_T_ and *μ*_C_ are the mean of the test group and the control group, respectively, and *σ* is the standard deviation (assuming the standard deviation of the two groups is the same). In addition, *α* and *β* are type I errors and type I errors, respectively. *K* is the distribution ratio of the number of cases between the experimental group and the control group. The study is required to have a probability of > 5% I errors and 20% II errors, so *α* = 0.05 and *β* = 0.2 [19]. According to previous studies, *μ*_T_ = 0.85, *μ*_C_ = 0.5, and *σ* = 1.4. Based on the pre-experimental results and an estimated missing follow-up rate of 10%, the final number of cases included is 266.

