## Evaluation

### Primary outcome

Effective rate of a 1% decrease in HbA1c and 3% decrease in body weight.

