### Statistical analysis methods

The data of this clinical trial will be analysed using SPSS Statistics 26.0 statistical software. First, the baseline situation of the two groups of patients will be analysed to ensure that the baseline of the treatment group and the control group are balanced. Normal tests will be performed for measurement data. Continuous variables conforming to a normal distribution will be represented by the mean and standard deviation. Two-independent sample *t*-tests will be used for two groups that conform to a normal distribution, and paired sample *t*-tests will be used for comparison of the same sample before and after comparison. Counting data will be represented by percentages, and the chi-square test will be adopted. For continuous variables that do not conform to the normal distribution, the median will be used, and the independent sample Wilcoxon rank sum test will be used for the two groups. The paired sample Wilcoxon rank sum test will be used for the comparison of the same sample before and after. The Wilcoxon rank sum test will also be used for ranked data. *P* ≤ 0.05 will be considered statistically significant.

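### The trial is sized for a difference in means of an unnamed variable, but the primary outcome is a responder rate, so the implied 80% power does not belong to the primary test

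*Protocol article*

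**What the plan says.** Three parts of the protocol article bear on this.

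- **Sample size calculation.** The section opens with "Our aim is to select an estimation method for sample size when comparing two sample means". It prints a two-means formula and defines its result as a number that "represents the estimated sample size of each test group". The inputs are alpha 0.05, beta 0.2, means of 0.85 (test) and 0.5 (control) and a common SD of 1.4, all attributed to previous studies. With 10% loss, the total is given as 266. Neither the variable nor its unit is named.
- **Primary outcome** (under Evaluation, and in the Abstract). "Effective rate of a 1% decrease in HbA1c and 3% decrease in body weight". This is a proportion of participants.
- **Statistical analysis methods.** "Counting data will be represented by percentages, and the chi-square test will be adopted". The significance threshold is P ≤ 0.05, with no statement of sidedness.

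Allocation is equal ("participants will be randomly assigned in a 1:1 ratio"), so 266 means 133 per arm, or about 120 per arm after 10% loss. The article assumes no responder rate for either arm.

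**The concern.** A sample size supports a power claim only for the variable and test it was computed for. Here the calculation concerns a continuous variable, while the test that decides the trial compares two proportions. The power of that test depends on the responder rate in each arm, and the article gives neither. The 80% implied by beta 0.2 is therefore attached to an analysis that is not the primary one.

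What is at stake is how the result is read. If the chi-square test is not significant, the reader will take it that the trial had an 80% chance of detecting the effect it was planned for, and nothing in the article supports that.

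**Working it through.** **1. The plan's own figure.** Inputs from the sample size section: difference 0.85 − 0.5 = 0.35, SD 1.4, K = 1, alpha 0.05, power 0.80. The margin term in the formula has no stated value and is taken as 0 (superiority over placebo).

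n per arm = 2 × SD² × (z_alpha + z_beta)² / difference²

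- One-sided, as the formula prints it (z at 1 − alpha): 2 × 1.96 × 2.4865² / 0.1225 = 197.8, so 198 per arm. After 10% loss, 198/0.9 = 220 per arm, 440 in total.
- Two-sided: 2 × 1.96 × 2.8016² / 0.1225 = 251.2, so 252 per arm. After loss, 280 per arm, 560 in total.

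Neither gives 133 per arm. The figure of 266 appears one-sided if the denominator is 0.45 instead of 0.35: 2 × (1.4 × 2.4865/0.45)² = 119.7, and 119.7/0.9 = 133.0. That would need a margin of −0.10, which the article does not state.

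**2. Power of the means comparison at the planned size.** With 120 evaluable per arm, the standard error is 1.4 × √(2/120) = 0.1807 and 0.35/0.1807 = 1.936.

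- Two-sided: Φ(1.936 − 1.960) = 49%.
- One-sided: Φ(1.936 − 1.645) = 61%.

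With all 133 per arm the figures are 53% and 65%.

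**3. Illustration for the HbA1c component.** Assumptions not in the article: the inputs are falls in HbA1c in percentage points, they are normally distributed, response is a fall of at least 1 point, and the weight criterion is ignored.

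- Test arm: 1 − Φ((1 − 0.85)/1.4) = 1 − Φ(0.107) = 45.7%.
- Control arm: 1 − Φ((1 − 0.5)/1.4) = 1 − Φ(0.357) = 36.0%.
- Difference: 9.7 points.

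Two-proportion test with pooled variance under the null:

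| | Power, 120 per arm | Power, 133 per arm | Evaluable per arm for 80% |
|---|---|---|---|
| Two-sided 5% | 33% | 36% | 404 |
| One-sided 5% | 45% | 48% | 318 |

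**4. The joint outcome.** Requiring the weight criterion as well needs weight-responder rates and their correlation with HbA1c response, and the article gives neither. Keep the step 3 HbA1c rates, assume control weight-responder rates of 30% to 70%, test-arm rates 0 to 20 points higher, and correlation 0 to 0.6. Two-sided power at 120 per arm then runs from about 8% to 71%. This range reflects assumed inputs and shows only that the article does not fix the answer.

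**5. What 266 can deliver for a proportion.** At 120 evaluable per arm and two-sided 5%, 80% power requires:

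| Control rate | Difference needed (points) |
|---|---|
| 10% | 13.4 |
| 15% | 15.0 |
| 20% | 16.2 |
| 30% | 17.5 |
| 40% | 18.0 |

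**The case against.** The strongest objection concerns how far the figures can be pushed, and most of it stands.

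- **One-third power as a finding.** A reader might infer that the stated inputs give the primary analysis about 33% power. They do not by themselves. The figure needs the unnamed variable to be HbA1c fall, normality, a two-sided test and no weight criterion. Read one-sided, as the formula is printed, it is 45%. It also describes one component, not the joint outcome.
- **Dichotomising as the sole cause.** A reader might blame the whole shortfall on the change from a mean to a rate. Under the illustration that change costs about 16 points (49% to 33%, two-sided). The gap between 80% and 49% arises because 266 does not follow from the stated inputs.
- **An inflated false-positive rate.** Reading the outcome as two separate rates with success on either, a reader might infer an error rate of up to 1 − 0.95² = 9.75%. No section states an either-component rule. The article uses the singular for the outcome, and one composite is the natural reading.
- **A missing time point.** The outcome section names no visit, but the schedule figure is not shown, this is a condensed article, and treatment ends at week 24. This alone is no defect.
- **0.85 and 0.5 as responder rates.** Power would then exceed 99%, but the text calls them means and gives an SD of 1.4.

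None of this restores the link between the calculation and the primary test. The article prints a complete formula, its inputs and a result, so this is not detail left to a fuller document.

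**Conclusion.** The point holds as a mismatch between sizing and primary analysis, and it needs correcting. The trial is sized on two means of an unnamed variable, the primary outcome is a proportion for a chi-square test, and no responder rates are assumed. This part needs no assumption. The 80% power implied by beta 0.2 does not apply to the deciding test.

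The actual power for the joint HbA1c-and-weight outcome cannot be determined from the article. The 33% two-sided (45% one-sided) figure is an illustration under the assumptions listed above. Separately, the stated inputs do not support 266 even for the means comparison: 80% power needs 252 evaluable per arm two-sided, or 198 one-sided, against about 120 available.

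**What to change.** 1. State the primary outcome as one test: the proportion meeting both thresholds at the end of treatment (week 24), compared by chi-square, with its sidedness given.
2. Replace the two-means calculation with a two-proportion one that uses a justified responder rate for each arm.
3. If enrolment stays at 266, restate what it delivers: with about 120 evaluable per arm and a two-sided 5% test, 80% power for a difference of about 16 to 18 points if the control rate is 20% to 40%, or about 13 to 15 points if it is 10% to 15%. Say whether a difference of that size is plausible.
4. Name the variable and unit behind 0.85, 0.5 and 1.4. If it is HbA1c change, the baseline-adjusted mean change at week 24 could optionally be reported as a supporting analysis. It should not be described as adequately powered.

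The cost is rewording the sample size and primary outcome sections and, if chosen, one added supporting analysis. Nothing changes in enrolment or conduct unless the sponsor decides to enrol more. The stated power will look less favourable.

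### The sample size is planned at a one-sided 5% critical value (1.645) but the primary rate is tested by chi-square at P ≤ 0.05 (in effect 1.96), so the planned power is overstated

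*Protocol article*

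**What the plan says.** The protocol article deals with type I error in two places.

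- **Sample size calculation.** The formula for comparing two means carries the term "Z_{1-\alpha}+Z_{1-\beta" (the quote stops before the closing brace). The text then reads "The study is required to have a probability of > 5% I errors and 20% II errors", and the same sentence goes on to set alpha to 0.05 and beta to 0.2. The other inputs are means of 0.85 and 0.5, an SD of 1.4, 10% loss to follow-up and a total of 266. The formula also subtracts a triangle term that is neither defined nor given a value.
- **Statistical analysis methods.** For rates: "Counting data will be represented by percentages, and the chi-square test will be adopted". For normally distributed continuous outcomes: "Two-independent sample *t*-tests will be used for two groups that conform to a normal distribution". A P value of 0.05 or less "will be considered statistically significant".

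The primary outcome is "Effective rate of a 1% decrease in HbA1c and 3% decrease in body weight", so it falls under the chi-square rule. Neither section says one-sided or two-sided.

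**The concern.** Z at 1 − alpha with alpha = 0.05 is 1.645, the critical value of a one-sided 5% test. A chi-square test on one degree of freedom has no direction: P ≤ 0.05 means a statistic of at least 3.84, which is |z| ≥ 1.96. The trial is thus sized for one threshold while its primary outcome is tested at a stricter one.

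What is at stake is power. The design section states a 20% type II error. If the number was derived at 1.645 and the result is judged at 1.96, the real type II error on the same assumptions is larger. A reader who takes the stated 80% power at face value is misled about the chance that a real effect will be missed.

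**Working it through.** **Inputs**, all from the sample size section unless noted: difference 0.85 − 0.5 = 0.35; SD 1.4; alpha 0.05; power 80% (Z = 0.8416); K = 1 (1:1 allocation, Randomization section); 10% loss; total 266, or 133 per arm. The margin (triangle) is not given, so any value for it is an assumption.

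**Step 1: critical values.** One-sided 5%: 1.645 (squared, 2.71). Two-sided 5%: 1.960 (squared, 3.84). The formula uses the first, the chi-square rule in effect the second.

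**Step 2: can 266 be reproduced?** With K = 1,

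n per arm = 2 × 1.4² × (Z for alpha + 0.8416)² / (0.35 − margin)², then divided by 0.9 for loss.

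| Margin (assumed) | Z for alpha | n evaluable per arm | n / 0.9 per arm |
|---|---|---|---|
| 0 | 1.645 | 197.8 | 220 |
| 0 | 1.960 | 251.2 | 280 |
| −0.1 | 1.645 | 119.7 | 133 |
| −0.1 | 1.960 | 151.9 | 169 |

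In the two margin-0 rows n is rounded up to 198 and 252 before the division. With margin 0 neither threshold gives 133 per arm. With a margin of −0.1 the formula as printed gives 119.68 / 0.9 = 132.98, so 133 per arm and 266 in total. Rounding 119.68 up to 120 first would give 133.3, so 134. At 1.960 the same margin gives 169 per arm, 338 in total. A two-sided calculation reaches 266 only with a margin near −0.16.

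**Step 3: power at the planned size.** Evaluable per arm: 133 × 0.9 = 119.7, taken as 120. Standard error of the difference: 1.4 × √(2/120) = 0.1807.

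- Margin 0: 0.35 / 0.1807 = 1.936. At 1.645, power = Φ(1.936 − 1.645) = 61%. At 1.960, power = Φ(1.936 − 1.960) = 49%.
- Margin −0.1: 0.45 / 0.1807 = 2.490. At 1.645, power = Φ(2.490 − 1.645) = 80%. At 1.960, power = Φ(2.490 − 1.960) = 70%.

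The change of threshold costs 12 percentage points in the first case and 10 in the second. The margin −0.1 case isolates the effect of sidedness on the calculation that yields 266. The analysis section mentions no margin, so the margin 0 case is closer to a test of no difference.

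**The case against.** Several points on the other side stand.

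- **There is one success rule, not two.** A reader might infer that a result with z between 1.645 and 1.96 is positive by the design section and negative by the analysis section, so that the sponsor could choose. The article does not support this. The sample size section plans a number and never declares a result positive. Only the analysis section says when a result is significant. For example, 40/133 against 54/133 responders (assumed counts) gives an uncorrected chi-square P of 0.073, which is not significant under the only written rule.
- **The inequality sign is a slip.** Read alone, a type I error above 5% sets no upper limit. But the same sentence goes on to set alpha to 0.05, so it is not a separate statement of alpha. It also says nothing about sidedness; that comes from the formula.
- **Two-sidedness is implied, not written.** For the chi-square test the inference is sound. For the t and Wilcoxon tests the tails are left open. An unstated side may be settled in an analysis plan that is not shown, so the missing word alone is no finding.
- **The margin of −0.1 is an inference.** With a free margin either threshold can be made to give 266. The value −0.1 is attractive because it is round and fits the formula as printed, but nothing in the article confirms it.

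None of this removes the mismatch. The article itself prints both the 1.645 formula and the chi-square rule, and they do not belong to the same test.

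**Conclusion.** The point holds as a mismatch between planning and testing. The formula uses a one-sided 5% critical value, the primary rate is tested in effect at two-sided 5%, and the power implied by beta = 0.2 is overstated for that test.

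The size depends on the undefined margin. Under either margin tried, power at the 1.96 threshold is below 80%. The figures rest on the printed means and SD, 120 evaluable per arm and the normal approximation. They do not give the power of the primary test, because the article states no response rates. The undefined margin and the use of a means formula for a rate endpoint are separate matters.

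**What to change.** Use one statement of type I error in both sections.

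1. In the sample size section, replace the inequality with a two-sided type I error of 5% and write the formula with Z at 1 − alpha/2.
2. In the statistical analysis methods, state that tests are two-sided and that a two-sided P ≤ 0.05 is significant.
3. Restate the power that 266 participants give at that alpha, with the value used for the triangle term.

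This changes wording only and adds no patients or procedures. The cost is a less favourable stated power: on the printed mean inputs, about 49% with margin 0 or 70% with margin −0.1. If the sponsor wanted to keep 80% power at two-sided 5% on those inputs, the total would be 560 or 338 respectively, which is a separate decision.

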Traditional Chinese medicine compounds have the characteristics of multicomponent, multilink and multichannel action, have a variety of pharmacological effects and play a therapeutic role in many key links of diseases [16]. DDG has become department cipher prescription based on long time clinical verification (specific prescription: *Atractylodes lancea* 18 g, *Atractylodes macrocephala* 18 g, *Salvia miltiorrhiza* 15 g, *Polygonum cuspidatum* 12 g, Folium ilicis cornutae 15 g, *Scutellaria* 12 g, *Linderae radix* 9 g). In our previous clinical studies, 80 subjects of T2DM with obesity were recruited, and the intervention treatment of traditional Chinese medicine DDG combined with metformin was conducted for 13 weeks using self-controlled experimental study methods before and after. The results showed that after 13 weeks of intervention, patients exhibited increased weight loss; glycosylated haemoglobin, fasting plasma glucose (FPG) and postprandial plasma glucose levels were decreased; triglycerides, low-density lipoprotein and free fatty acid levels were improved; and high-density lipoprotein levels were increased. DDG also improves insulin resistance in patients, reduces body weight and blood lipids while lowering glucose levels, improves the quality of life of patients and plays roles in comprehensive prevention and treatment. More importantly, during the 13-week intervention, no serious adverse effects were detected. And only 2 cases had adverse effects of diarrhea, and all completed the trial. The relevant achievements have been patented (Application No. 201710563974.4) and are now in the stage of substantive examination.

Therefore, based on a multicentre randomized, double-blind clinical study design, this study aims to sufficiently verify that DDG combined with metformin is effective and safe as an intervention in patients who have T2DM with obesity, laying a foundation for providing valuable new drugs for clinical use.

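### The printed sample-size inputs do not give 266: with no margin they need 440 (one-sided) or 560 (two-sided), so the stated 20% type II error is not delivered for the mean used in the calculation

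*Protocol article*

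**What the plan says.** The Sample size calculation section begins: "Our aim is to select an estimation method for sample size when comparing two sample means". Its formula multiplies the squared sum of Z at 1−α and Z at 1−β by the variance and by (1 + 1/K), then divides by the square of the mean difference less a margin, printed as a triangle. The text explains the means, the standard deviation, α, β and K. It neither explains the triangle nor gives it a value.

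The error rates are given as "so *α* = 0.05 and *β* = 0.2". The remaining inputs are: "According to previous studies, *μ*_T_ = 0.85, *μ*_C_ = 0.5, and *σ* = 1.4". The variable and its units are not named. The section ends: "Based on the pre-experimental results and an estimated missing follow-up rate of 10%, the final number of cases included is 266". The Abstract splits this into 133 per group, and the Randomization section confirms that "participants will be randomly assigned in a 1:1 ratio".

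Statistical analysis methods plans ordinary t, chi-square and Wilcoxon tests. The significance rule is that P at or below "0.05 will be considered statistically significant". No margin and no one-sided test is mentioned. The Introduction gives the aim as verifying that the granules added to metformin are effective and safe. The primary outcome is an effective rate, that is, the proportion of participants who meet an HbA1c and body-weight threshold.

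**The concern.** The section prints a formula, its inputs and a result, so a reader should be able to get from one to the other. The missing margin blocks that. With the value that an efficacy comparison against placebo would normally take, zero, the result is far above 266.

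What is at stake is the stated 20% type II error. If it is not delivered, a non-significant result on the variable behind the calculation would be read as coming from a study with 80% power when the true figure is well below that.

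**Working it through.** **Inputs.** From Sample size calculation: difference 0.85 − 0.5 = 0.35; SD 1.4; α 0.05; β 0.2; loss 10%. From Randomization: 1:1, so K = 1. Assumption: Δ = 0, because the protocol gives no value, states an efficacy aim and plans tests without a margin.

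**Formula per arm.** n = (Zα + 0.8416)² × 1.4² × 2 / (0.35 − Δ)², where 1.4² × 2 = 3.92.

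**Attempt to reproduce 266 with Δ = 0**
- One-sided, as printed (Zα = 1.6449): 6.1826 × 3.92 / 0.1225 = 197.84, so 198 per arm and 396 evaluable. 396/0.9 = 440.
- Two-sided (Zα = 1.9600): 7.8489 × 3.92 / 0.1225 = 251.16, so 252 per arm and 504 evaluable. 504/0.9 = 560.
- Adding 10% instead of dividing by 0.9 gives 436 or 555.
- Reading the per-arm result as a total gives 197.84/0.9 ≈ 220 or 251.16/0.9 ≈ 279.
- Reading 0.85 and 0.5 as proportions gives 49 to 74 in total.

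None of these is 266.

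**Effect of the margin**
- Positive Δ raises n. At Δ = +0.1, one-sided: 6.1826 × 3.92 / 0.25² = 387.77 per arm, about 862 in total after loss.
- Negative Δ lowers n. At Δ = −0.1, one-sided: 6.1826 × 3.92 / 0.45² = 119.68 per arm, and 119.68/0.9 = 132.98, so 133 per arm and 266 in total.
- This is not the only match. A two-sided test with Δ of about −0.157 gives 7.8489 × 3.92 / 0.507² ≈ 119.7 per arm, again 133 after loss.

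**Power for a true difference of 0.35 with SD 1.4 and Δ = 0.** The standard error is 1.4 × √(2/n). Ten per cent loss leaves 133 × 0.9 = 119.7, taken as 120 per arm.

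| Evaluable per arm | SE | 0.35/SE | Two-sided 0.05 | One-sided 0.05 |
|---|---|---|---|---|
| 120 | 0.1807 | 1.936 | Φ(1.936 − 1.960) = 49% | Φ(1.936 − 1.645) = 61% |
| 133 | 0.1717 | 2.039 | Φ(2.039 − 1.960) = 53% | Φ(2.039 − 1.645) = 65% |

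A noncentral-t calculation gives the same figures to within half a percentage point.

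**Difference detectable with 80% power at 120 per arm**
- Two-sided: 0.1807 × (1.960 + 0.842) = 0.51.
- One-sided: 0.1807 × (1.645 + 0.842) = 0.45.

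**The case against.** Four points can be made for the protocol or against a stronger reading.

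1. **The trial's power is not 49%.** A reader might infer that the trial as a whole has 49% power. The documents do not support that. The primary outcome is a responder rate, while the calculation concerns an unnamed mean, so power for the primary test cannot be computed from the protocol. This stands.
2. **49% is the lowest of four figures.** It assumes a two-sided test, which is the usual convention but is not stated, and it assumes that everyone lost also leaves the analysis. The full analysis set keeps dropouts with at least one follow-up, and missing values are carried forward, so the number analysed could lie between 120 and 133 per arm, although rejected cases are removed. This stands as well, and the range to quote is 49% to 65%. All of it is below 80%.
3. **The origin of 266 is not shown.** A reader might conclude that a non-inferiority margin of 0.1 was used. It reproduces the figure exactly, but other negative margins do so with a two-sided test, and the document states none. What is firm is that the margin is unstated and that no margin of zero or above gives 266.
4. **The control mean may have a source.** The one earlier study described was "conducted for 13 weeks using self-controlled experimental study methods before and after", so it had no control arm. A reader might infer that 0.5 has no basis. However, the section refers to previous studies in the plural, so another source is not ruled out. Only the absence of an identified source can be asserted.

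None of these points recovers 266 from the printed inputs at 80% power.

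**Conclusion.** The figure is wrong as written. With a zero margin, the printed inputs need 440 participants one-sided or 560 two-sided. The stated 266 is about 60% of the first (266/440) and 48% of the second (266/560). For a difference of 0.35 in the unnamed mean with SD 1.4, the type II error is 35% to 51%, against the stated 20%.

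The conclusion rests on Δ = 0, which follows from the efficacy aim and the margin-free tests, and on the printed means, SD and error rates. It does not depend on sidedness, which changes only the size of the shortfall. A negative margin would rescue the arithmetic, but it would size the trial for a hypothesis that the planned analysis does not test.

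**What to change.** Keep 266 and correct the section so that it says what this number delivers.

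- State Δ = 0, and state that α is two-sided 0.05, in line with the planned tests.
- Name the variable, its units and the source of 0.85, 0.5 and 1.4, including where the control mean comes from.
- Replace the 20% type II error with the two-sided power for that mean: about 49% for a difference of 0.35 at 120 evaluable per arm, 53% with no loss, or 80% for a difference of about 0.51 at 120 per arm.
- Say that this figure does not describe power for the primary responder rate. State that power separately, from the responder rates expected in each arm.

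The cost is a rewritten section and a less favourable stated power. Restating the figure for the mean needs no extra participants. What the separate responder-rate calculation will show cannot be foreseen from the protocol.
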